## Abstract

**Background:**

Pulmonary rehabilitation is widely recommended to improve functional status and as secondary and tertiary prevention in individuals with chronic pulmonary diseases. Unfortunately, access to timely and appropriate rehabilitation remains limited. To help close this inaccessibility gap, telerehabilitation has been proposed. However, exercise testing is necessary for effective and safe exercise prescription. Current gold-standard tests, such as maximal cardiopulmonary exercise testing (CPET) and the 6-minute walk test (6MWT), are poorly adapted to home-based or telerehabilitation settings. This was an obstacle to the continuity of services during the COVID-19 pandemic. It is essential to validate tests adapted to these new realities, such as the 6-minute stepper test (6MST). This test, strongly inspired by 6MWT, consists of taking as many steps as possible on a “stepper” for 6 minutes.

**Objective:**

This study aims to evaluate the metrological qualities of 6MST by (1) establishing concurrent validity and agreement between the 6MST and CPET, as well as with the 6MWT; (2) determining test-retest reliability in a home-based setting with direct and remote (videoconferencing) monitoring; and (3) documenting adverse events and participant perspectives when performing the 6MST in home-based settings.

**Methods:**

Three centers (Centre de recherche de l’Institut universitaire de cardiologie et de pneumologie de Québec in Québec, Groupement des Hôpitaux de l’Institut Catholique de Lille in France, and FormAction Santé in France) will be involved in this multinational project, which is divided into 2 studies. For study 1 (objective 1), 30 participants (Québec, n=15; France, n=15) will be recruited. Two laboratory visits will be performed to assess anthropometric data, pulmonary function, and the 3 exercise tolerance tests (CPET, 6MWT, and 6MST). Concurrent validity (paired sample t tests and Pearson correlations) and agreement (Bland-Altman plots with 95% agreement limits) will be evaluated. For study 2 (objectives 2 and 3), 52 participants (Québec, n=26; France, n=26) will be recruited. Following a familiarization trial (trial 1), the 6MST will be conducted on 2 separate occasions (trials 2 and 3), once under direct supervision and once under remote supervision, in a randomized order. Paired sample t test, Bland-Altman plots, and intraclass correlations will be used to compare trials 2 and 3. A semistructured interview will be conducted after the third trial to collect participants’ perspectives.

**Results:**

Ethical approval was received for this project (October 12, 2023, in Québec and September 25, 2023, in France) and the first participant was recruited in February 2024.

**Conclusions:**

This study innovates by validating a new clinical test necessary for the development and implementation of new models of rehabilitation adapted to home and telerehabilitation contexts. This study also aligns with the United Nations Sustainable Development Goals by contributing to augmenting health care service delivery (goal 3) and reducing health care access inequalities (goal 11).

**Trial Registration:**

ClinicalTrials.gov NCT06447831; https://clinicaltrials.gov/study/NCT06447831

**International Registered Report Identifier (IRRID):**

DERR1-10.2196/57404

## Introduction

### Background

Recent guidelines strongly recommend pulmonary rehabilitation for individuals with stable or acutely exacerbated chronic obstructive pulmonary disease (COPD) or with interstitial lung disease (ILD) [1]. Unfortunately, access to rehabilitation care remains limited in many countries, including Canada and France. Indeed, the latest available estimates indicate that only 0.4% of individuals in Canada and 8.6% of individuals in France with COPD have access to pulmonary rehabilitation programs [2,3]. The development of new and innovative health care models, including in rehabilitation, is urgently needed to address this health care gap that is only expected to worsen with the aging populations in most advanced economies [2,4]. Home-based rehabilitation and telerehabilitation are now increasingly considered as a solution to increase rehabilitation access in this population [1,4,5]. These programs are cost-effective alternatives to traditional ambulatory pulmonary rehabilitation models anchored in specialized hospital institutions [6,7]. Moreover, the effectiveness of home-based rehabilitation and pulmonary telerehabilitation programs has been demonstrated and is comparable to traditional rehabilitation models in individuals with COPD [8]. Yet, clinicians report the lack of validated functional exercise capacity tests for these new models of care as a major barrier for their implementation [9,10]. These tests are important to ensure safe, effective, and personalized exercise prescription during rehabilitation, and to monitor and document its effects [11,12].

The current gold standard for exercise capacity testing is maximal cardiopulmonary exercise testing (CPET), which is generally conducted on a cycle ergometer or a treadmill. These tests are designed to assess maximal physiological responses to exercise and thus require expensive equipment (eg, gas exchange analyzer and electrocardiogram) that are not easily accessible outside of specialized institutions. Moreover, these tests are not always representative of functional activities in daily life (eg, cycling may not be an activity of daily life for many individuals) [13]. Thus, functional capacity tests have been widely adopted in ambulatory rehabilitation settings [13,14]. To this effect, the 6-minute walk test (6MWT), which only requires an unobstructed corridor (≥30 meters), is among the most widely used [13,15]. Despite its simplicity, the 6MWT is not adapted to the realities of home-based and telerehabilitation settings. Indeed, limited available space inhibits its realization and has been highlighted as a barrier to the continuity of rehabilitation services during the COVID-19 pandemic [9]. It is therefore essential to validate functional capacity tests adapted to this new reality, such as the 6-minute stepper test (6MST). This test, strongly inspired by 6MWT, consists of taking as many steps as possible on a “stepper” for 6 minutes [16,17].

In individuals with COPD, initial studies indicate that the 6MST is reliable, as no significant difference in test results was found when repeated on consecutive days in a laboratory setting [16]. The 6MST is also valid, as the number of steps taken during the test is correlated with the total distance traveled during the 6MWT (*r*=0.56-0.87, *P*<.01), peak power during CPET (*r*=0.46, *P*<.01), and peak oxygen consumption during CPET (*r*=0.39, *P*<.01) [17,18]. Responsiveness to change following pulmonary rehabilitation has also been shown, with a minimally important difference estimated at 40 steps [19]. Finally, predictive equations have been computed to individualize aerobic training intensity using the 6MST [20]. However, to our knowledge, cardiorespiratory responses during the 6MST in individuals with COPD have not been formally compared with those during the 6MWT and CPET to date. This is particularly important when considering the development of home-based and telerehabilitation programs, as different cardiorespiratory responses to testing may elicit safety concerns. In individuals with ILD, there is limited evidence regarding the validity of the 6MST, as the number of steps taken during the test is correlated with the total distance traveled during the 6MWT (*r*=0.70, *P*<.01) [21]. Interestingly, in individuals with ILD, cardiorespiratory responses during the 6MST have been compared with the 6MWT. In this population, the 6MST leads to greater heart rate and ventilatory responses, and blood oxygen saturation remains higher during the 6MST [21,22]. Finally, as the 6MST has only been validated in laboratory or hospital settings, metrological properties in home-based settings with direct or remote (ie, videoconferencing) monitoring are currently unknown in individuals with COPD or ILD.

### Objectives and Hypotheses

#### Overview

The overall aim of this project is to provide further evidence regarding the metrological properties of the 6MST in individuals with COPD or ILD. Specific objectives and hypotheses are described below.

#### Objective 1

Objective 1 is to determine concurrent validity and the level of agreement (or bias) between peak cardiorespiratory responses and reported symptomology during the 6MST and CPET and the 6MST and 6MWT. The corresponding hypotheses are that peak cardiorespiratory responses and reported symptomology to the 6MST will be strongly correlated to those measured during CPET and the 6MWT (ie, concurrent validity), and that these values will be systematically lower than those measured during CPET (ie, presence of bias), but similar to those measured during the 6MWT (ie, no bias).

#### Objective 2

Objective 2 is to determine test-retest reliability for the 6MST in home-based settings under direct and remote (ie, videoconferencing) monitoring. The corresponding hypothesis is that measurement error will be minimal and intraclass correlations will be good and similar between direct and remote supervision.

#### Objective 3

Objective 3 is to determine the safety and the perception of the 6MST in individuals with chronic pulmonary diseases in home-based settings under direct and remote monitoring by collecting adverse events and qualitative feedback. The corresponding hypothesis is that the test will be safe (ie, absence of serious adverse events) and individuals will report a good level of overall satisfaction with the test, irrespective of the type of supervision.

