#### Second and Third Trials

The second and third trials of the 6MST will be performed in a randomized order, with either direct (therapist present at the home) or remote (therapist present through videoconferencing software, as in a telerehabilitation setting) monitoring. For the remotely monitored trial, another person (ie, family member, etc) will be present to ensure safety in case of emergency. The 6MST and adverse events will be, respectively, performed and collected as in the first trial (the only difference being the presence of the therapist through videoconferencing for one of the trials). The third trial of the 6MST will be followed by a semistructured interview using a guide created a priori. This interview will focus on the 2 themes, that are (1) level of comfort executing the test (ease of execution, symptoms, and anxiety) and (2) perception of safety (regarding test and home and telerehabilitation settings). The interview will be conducted in person or through videoconferencing software, depending on the randomization of the third trial.

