### Data Preparation and Analysis

All data will be stored in digital databases (REDCap [Research Electronic Data Capture] in Québec and OpenClinica in France) on secured servers at the participating research facilities (CR-IUCPQ and GHICL) following local protocols. Using a standardized thesaurus, research teams will enter data directly into both databases through remote access. With regard to data analysis, descriptive statistics will be used to summarize participant characteristics. For quantitative data, normality will be verified with Shapiro-Wilk tests and Q-Q plots. All statistical analyses will be completed using SPSS Statistics Version 28 (IBM) with a significance level set at *P*<.05. Graphical analyses will be conducted using Excel (version 2305; Microsoft Corporation) and qualitative analyses will be performed with Nvivio (version 14; Lumivero).

For objective 1, concurrent validity will be assessed using paired sample *t* tests (or Wilcoxon signed-rank tests) to verify whether peak cardiorespiratory (eg, oxygen consumption, minute ventilation, and heart rate) and symptomology (ie, dyspnea and leg fatigue) values obtained during the 6MST are comparable to the CPET and 6MWT. Pearson correlation coefficients (*r*) will also be calculated to quantify the strength of association between peak cardiorespiratory and symptomology values reached during the 6MST with those reached during the CPET and the 6MWT. Additional Pearson correlation coefficients (*r*) will be calculated to determine the strength of the association between the number of steps taken during the 6MST and peak oxygen consumption and heart rate reached during all 3 tests. The level of correlation will be interpreted as poor (≤0.20), fair (0.21-0.40), moderate (0.41-0.60), good (0.61-0.80), and very good (0.81-1.00) [41]. The agreement will be assessed with Bland-Altman plots and 95% limits of agreement (mean difference ± 1.96 SD of the difference) between peak cardiorespiratory and symptomology values reached during the 6MST and those reached during the CPET and the 6MWT [41].

For objective 2, reliability (trial 2 vs 3) will be assessed using paired sample *t* tests (or Wilcoxon signed-rank tests), Bland-Altman plots (with 95% limits of agreement), and intraclass correlations [42-44]. Intraclass correlations will be interpreted as poor (≤0.50), moderate (0.51-0.75), good (0.76-0.9), and very good (0.91-1.00) [44].

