### Strengths and Limitations

This research project has strengths and limitations that warrant consideration. With regard to strengths, first, sex parity will be assured and help limit bias, particularly related to the under-representation of people of the female sex in the pulmonary rehabilitation literature [46]. Second, the a priori calculation of sample sizes required will ensure sufficient statistical power to address the study’s objectives. Third, the inclusion of several different and complementary statistical strategies will ensure adequate evaluation of the metrological properties of the included tests. Fourth, the multicenter and multinational nature of this study will improve its external validity and generalizability. Fifth, the inclusion of a mixed methods study design will help ensure that stakeholders (ie, individuals with pulmonary diseases) have input regarding the acceptability and use of the physical tests being validated in this research project. Finally, the publication of this protocol a priori will ensure accountability and any changes made a posteriori will be public knowledge and require justification.

With regard to limitations, first, only individuals with COPD and an ILD will be included in this study. This will limit its generalizability in the population with other pulmonary diseases (eg, asthma and cystic fibrosis). This methodological choice was made in an effort to reconcile feasibility (limited time and budget) and generalizability (ie, heterogeneity). Second, for study 1, participants will be required to perform several physical tests on the same day, potentially leading to fatigue that may alter performances. To address this, tests occurring on the same day are separated by a rest period and are randomized. Moreover, the research team has extensive experience with this type of protocol. Finally, regarding test-retest reliability in study 2, a learning effect is possible as the test will be conducted repeatedly. To limit this effect, the first trial of the test will exclusively serve as a familiarization trial. In addition, a 2-minute warm-up period is allotted before each trial. Nonetheless, as the learning effect may not be completely eliminated, randomization of the second and third trials is performed in order to limit a systemic effect on the test conditions (ie, with a therapist present or through videoconferencing software).

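### Objective 2 hypothesises similar ICCs under direct and remote supervision, but with one trial per mode the design gives a single cross-mode ICC

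*Protocol article*

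**What the plan says.** Objectives and Hypotheses, Objective 2, sets out to "determine test-retest reliability for the 6MST in home-based settings under direct and remote (ie, videoconferencing) monitoring". The hypothesis is that "measurement error will be minimal and intraclass correlations will be good and similar between direct and remote supervision".

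The Abstract (Methods) has the test done, after a familiarization trial, "once under direct supervision and once under remote supervision, in a randomized order". Study 2, Second and Third Trials, confirms that only one trial is remote: "the only difference being the presence of the therapist through videoconferencing for one of the trials". Study 2, First Trial, has the therapist in the home for trial 1. Strengths and Limitations adds that "the first trial of the test will exclusively serve as a familiarization trial".

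Data Preparation and Analysis fixes the comparison: "reliability (trial 2 vs 3) will be assessed using paired sample" t tests (or Wilcoxon tests), Bland-Altman plots with 95% limits of agreement, and intraclass correlations. The sample size paragraph assumes a minimal acceptable ICC of 0.5, an expected ICC of 0.75, 80% power, alpha .05 and 15% dropout, and arrives at 52 participants taken as one group.

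**The concern.** Saying that ICCs are similar between two modes presupposes an ICC for each mode. Test-retest reliability under a mode needs at least two measurements under that mode. Trials 2 and 3 supply one of each, so the planned ICC measures how well a direct result and a remote result agree in the same person. That is a useful quantity, but it is not the one hypothesised.

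Two things are at stake. First, part of a stated hypothesis can be neither confirmed nor refuted by the data to be collected. Secondly, if the ICC comes out low, the study cannot say whether the stepper test is poorly repeatable or whether individuals respond differently to remote supervision. The article presents remote home testing as a novel contribution, so readers may take the trial 2 versus 3 ICC as the retest reliability of the remotely supervised test.

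**Working it through.** **1. Which pairs exist for each completer**

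| Order | Trial 1 (familiarization) | Trial 2 | Trial 3 | Remote–remote pair | Direct–direct pair |
|---|---|---|---|---|---|
| Direct first | direct | direct | remote | none | trials 1 and 2 |
| Remote first | direct | remote | direct | none | trials 1 and 3 |

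The planned pair (trials 2 and 3) is one direct and one remote in both rows. Splitting by order gives two ICCs, both cross-mode. Every completer, about 52 × 0.85 = 44, has a direct–direct pair. It always involves trial 1, which the article reserves for familiarization and which carries the learning effect.

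**2. What the stated sample size was built for**

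Walter-Eliasziw-Donner formula: n = 1 + 2k(z_α + z_β)² / [(k − 1)(ln C₀)²], with C₀ = (1 + kθ₀)/(1 + kθ₁) and θ = ρ/(1 − ρ).

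- ρ₀ = 0.5 gives θ₀ = 1; ρ₁ = 0.75 gives θ₁ = 3.
- k = 2: C₀ = 3/7, and (ln C₀)² = 0.718.
- Two-sided alpha .05, power 80%: (1.960 + 0.842)² = 7.85.
- n = 1 + 4 × 7.85 / 0.718 = 44.7, so 45.
- With 15% dropout: 45 × 1.15 = 51.8, so 52; or 45 / 0.85 = 52.9, so 53.

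The stated 52 is reproduced. One-sided with k = 2 gives 36 before dropout and 43 after (dividing by 0.85); two-sided with k = 3 gives 30 and 36, and with k = 4 gives 24 and 29. None of these matches. The figure fits one ICC on two measurements per person.

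**3. What that ICC identifies**

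Let a result under mode m be the mode mean plus a person effect S, a person-by-mode effect I_m and a retest error e_m, with total variance 1 in each mode.

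- Cross-mode ICC (no mean shift) = σ²_S.
- Within-mode ICC = σ²_S + σ²_I,m.
- One trial per mode shows only the sum σ²_I,m + σ²_e,m, so the within-mode ICC cannot be recovered.

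Illustration with an assumed σ²_S = 0.70:

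| Within-mode ICC (direct, remote) | σ²_I, σ²_e direct | σ²_I, σ²_e remote | Mean trial 2 vs 3 ICC (SD), simulated, n = 44 |
|---|---|---|---|
| 0.75, 0.75 | 0.05, 0.25 | 0.05, 0.25 | 0.69 (0.08) |
| 0.95, 0.70 | 0.25, 0.05 | 0.00, 0.30 | 0.69 (0.08) |
| 0.75, 0.95 | 0.05, 0.25 | 0.25, 0.05 | 0.69 (0.08) |

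Equal and clearly unequal within-mode reliabilities give the same planned statistic.

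**4. What a good value would still imply**

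With independent errors, the cross-mode correlation cannot exceed √(R_direct × R_remote). At 0.75 the product is at least 0.75² = 0.5625. The pair may be (0.75, 0.75) or as far apart as (1.00, 0.56), a gap of 0.44. With 44 completers, the 95% interval around an ICC of 0.75 (one-way F distribution, k = 2) is 0.59 to 0.86. At the lower limit the product need only reach 0.59² = 0.35.

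**The case against.** The operative plan is coherent. The Abstract, the analysis section and the sample size all point to one comparison of trials 2 and 3, and the paired test, limits of agreement and ICC do address whether the two modes give similar results. On that looser reading the hypothesis is testable. This stands, and it is why the correction is confined to wording. The sentence as written, however, speaks of ICCs being similar, and the objective speaks of reliability under each mode.

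A second argument is that a high cross-mode ICC supports remote reliability indirectly. If the true value were 0.75 and direct reliability were perfect, remote reliability would still be at least 0.56, above the article's minimum of 0.5. This also stands in part. It needs independent errors, it weakens once sampling error is allowed for, and it bounds a product without showing that the two factors are similar.

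A third is that mode-specific error variances can be estimated from one trial per mode if true scores are identical in both modes and errors independent. That assumes away the person-by-mode interaction, which is part of the question, and the article plans no such analysis.

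A reader might go further than the documents allow in four ways:
- That the whole hypothesis is untestable. Minimal measurement error and a good cross-mode ICC can be examined as planned, as can systematic bias between modes.
- That direct–direct pairs exist only in the half allocated to direct supervision first. Trial 1 is direct, so every completer has one; the limitation is its role and the learning effect.
- That the sample size is wrong. It is reproduced for a single two-measurement ICC.
- That nothing could be said about remote reliability. A high cross-mode ICC is indirect evidence, as shown.

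**Conclusion.** The hypothesis is wrong as written in one clause, and the label of objective 2 promises more than the design can give. There are no remote–remote pairs, so neither a remote ICC nor its similarity to a direct ICC can be estimated; because the data will not exist, no separate analysis plan can repair this. The planned ICC is a cross-mode ICC in which retest error and person-by-mode interaction are inseparable. A mean shift between modes is not hidden, because the paired test and the Bland-Altman bias would show it.

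The absence of remote repeats follows from the design alone. The compatible gap of up to 0.44 at a cross-mode value of 0.75 assumes independent errors and ignores sampling error. The 0.70 in the illustration is an assumed value, not a figure from the article. No error in the sample size or in the planned analyses follows from this point.

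**What to change.** Restate objective 2 and its hypothesis, and the matching objective in the Abstract, as reliability and agreement of the 6MST between direct and remote home supervision, with one trial under each. Delete the clause on similarity between modes. In Data Preparation and Analysis, label the trial 2 versus 3 ICC as a cross-mode ICC and state that it combines retest error with any person-by-mode interaction.

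The 52 participants, the visits and the planned analyses stay as they are. The cost is a narrower claim: the study will not report test-retest reliability within remote supervision. The Results section places study 2 recruitment after completion of study 1, so on the stated timetable the wording can change before study 2 data arrive.

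A comparison built on trial 1 should not be added as a substitute. It conflicts with that trial's stated role, is affected by learning, and still contains no remote repeat.

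Keeping the similarity hypothesis would be a different study: at least two non-familiarization trials per mode (or two parallel groups each repeating one mode), a margin for similar, and a new sample size. As an indication, with 44 completers doing two trials in each mode, both within-mode ICCs at 0.75 and a cross-mode correlation of 0.70 (all assumed), the simulated difference between the two ICCs has an SD of about 0.08, so a 95% interval of about ±1.96 × 0.08 = ±0.16.

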**Exclusion criteria**
Interstitial lung disease associated with connective tissue disease and sarcoidosis (often accompanied by multisystemic effects)Unstable or severe cardiac conditionInvalidating rheumatologic or neurologic conditionWeight exceeding maximal limits of exercise equipment (eg, 130 kg for the stepper)Any other physical or medical condition limiting or contraindicating exercise testingSimultaneous participation in another study requiring changes in medicationRecent pulmonary rehabilitation (≤1 year, potential learning bias for the 6-minute walk test and the 6-minute stepper test)For study 1 only: use of oxygen therapy (unable to provide oxygen therapy during testing due to limitation of gas exchange analysis equipment)For study 2 only: participation in study 1

For study 1, a mean difference of 0.28±0.32 L/min in maximal oxygen uptake between the 6MST and CPET was assumed, based on previous studies between the 6MWT and CPET [22,24]. To detect a difference of this amplitude with a paired sample *t* test, assuming a power of 80%, an α level of .05, and a dropout rate of 15%, 15 participants are needed. Fifteen individuals of each disease population (ie, COPD, n=15; ILD, n=15) will be included for a total sample of 30 participants (Québec, n=15; France, n=15), as cardiorespiratory responses to exercise are different among these populations [25].

For study 2, a minimal acceptable intraclass correlation coefficient of 0.5, and an expected intraclass correlation coefficient of 0.75, were assumed for the test-retest reliability of the 6MST. Assuming a power of 80%, an α level of .05, and a dropout rate of 15%, 52 participants (Québec, n=26; France; n=26) will be recruited. This calculated sample was taken as a whole, as test-retest reliability is not expected to be influenced by the type of respiratory disease.

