#### First Trial

The first trial of the 6MST (familiarization trial) will be conducted at the participant’s home with the therapist present. Preceding this trial, the Short Physical Performance Battery will be performed to obtain a general assessment of lower limb function [39].

The 6MST will be performed using a standardized portable stepper (same as in study 1) and following the same protocol as in study 1, including the 2-minute pretest warm-up period. However, full cardiorespiratory responses will not be measured. Instead, an oximeter (Nonin) will be used to monitor heart rate and SpO_2_ continuously. Blood pressure, dyspnea, and perceived exertion will be measured pre*-* and posttest using the modified Borg scale (/10). For individuals on home oxygen therapy, oxygen flows will be titrated if SpO_2_ falls below 88% during the test, with the aim of maintaining SpO_2_ between 88% and 92%, while always respecting the flow limits of the prescribing physician’s parameters. As in study 1, the test will be terminated if blood oxygen saturation falls to ≤80% accompanied by symptoms of hypoxia (such as dizziness, nausea, etc).

All adverse events will be recorded and graded according to the Common Terminology Criteria for Adverse Events, version 5 (United States Department of Health and Human Services), progressing from mild (1) to lethal (5) [40]. Textbox 5 presents the standardized grading used in this study. Adverse events are defined as any event that leads to (or could potentially lead to) prejudice to the participant or that inhibits the completion of the test. Examples include dyspnea, dizziness or nausea, close-call or fall events, musculoskeletal pain, chest pain, syncope, etc.

Classification of adverse events based on the Common Terminology Criteria for Adverse Events, version 5.

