For objective 3, all minor and serious adverse events, for all trials, will be reported. The semistructured interviews will be voice-recorded and transcribed. Thematic content analysis will be used to analyze all verbatim [45]. Briefly, a combination of deductive (based on a priori interview guide) and inductive (based on data) approaches will be used to generate themes and subthemes. Coding will be conducted separately by 2 reviewers, who will compare their results and resolve discrepancies through discussion.

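### Objective 3 equates safety with no serious adverse event, but zero events in 44–52 remote tests leaves risks up to about 6–8% open, and 'serious' is not tied to the 1–5 grades

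*Protocol article*

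**What the plan says.** Under Objectives and Hypotheses, objective 3 covers the safety and perception of the 6MST at home under direct and remote monitoring. Its hypothesis is that "the test will be safe (ie, absence of serious adverse events" and that participants will be satisfied, "irrespective of the type of supervision".

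The study 2 sample size, in the participants section, rests on "a minimal acceptable intraclass correlation coefficient of 0.5, and an expected intraclass correlation coefficient of 0.75". The text continues: "Assuming a power of 80%, an α level of .05, and a dropout rate of 15%, 52 participants" are to be recruited. No adverse-event rate appears in that calculation. Strengths and Limitations nevertheless credits the a priori sample sizes with giving enough power for the objectives of the study, without excepting objective 3.

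Under First Trial, events are graded with CTCAE version 5, "progressing from mild (1) to lethal (5". Textbox 5 labels the grades mild, moderate, severe, life-threatening and lethal. Table 2 uses two rows instead, minor and serious. For objective 3, Data Preparation and Analysis says that "all minor and serious adverse events, for all trials, will be reported".

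**The concern.** Two things do not fit together.

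First, the stated meaning of 'safe' is an observed count of zero in a sample chosen for a reliability coefficient. A count of zero in about 50 people is compatible with risks that may matter for a test intended for home and telerehabilitation use. If the hypothesis is reported as confirmed on those terms, the conclusion will be stronger than the data. The criterion also fails in the other direction: one serious event, related to the test or not, would contradict it.

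Second, the word that decides the hypothesis, 'serious', is not one of the five grades and is nowhere linked to them. Grade 3 is called severe, which is a different term. It groups hospitalisation, limits on self-care and syncope. Whether a grade 3 event such as syncope would defeat the hypothesis is left open.

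**Working it through.** **Inputs from the protocol**
- Recruited to study 2: 52. Dropout: 15%. Completers: 52 × 0.85 = 44.2, so about 44.
- Tests per participant: one familiarisation trial, then one direct and one remote trial in random order. All three are done at home.
- Remote tests: 44 to 52. All home tests: 3 × 44 = 132 to 3 × 52 = 156.
- Acceptable serious-event rate: none stated. The true risks used below are assumptions, shown as a range.

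**Reproducing the 52**

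The standard ICC formula (Walter, Eliasziw and Donner) with k = 2 trials, since "reliability (trial 2 vs 3) will be assessed", is n = 1 + 2(z_α + z_β)²k / [(ln C₀)²(k − 1)].
- θ₀ = 0.5/0.5 = 1 and θ₁ = 0.75/0.25 = 3.
- C₀ = (1 + 2·1)/(1 + 2·3) = 3/7, so (ln C₀)² = 0.718.
- With two-sided α 0.05 and 80% power, (1.960 + 0.842)² = 7.85.
- n = 1 + 2 × 7.85 × 2 / 0.718 = 44.7, so 45.
- Allowing for dropout, 45 × 1.15 = 51.75, so 52; or 45/0.85 = 52.9, so 53.

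The stated 52 reproduces to within one participant. It is an ICC sample size and contains no safety input.

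**What zero serious events would show**

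With zero events in n independent units, the exact upper limit is 1 − 0.05^(1/n) (one-sided 95%) or 1 − 0.025^(1/n) (upper end of the two-sided 95% Clopper-Pearson interval).

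| Units | n | One-sided | Two-sided |
|---|---|---|---|
| Remote tests, all recruited | 52 | 5.6% | 6.8% |
| Remote tests, completers | 44 | 6.6% | 8.0% |
| All home tests, all recruited | 156 | 1.9% | 2.3% |
| All home tests, completers | 132 | 2.2% | 2.8% |

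The last two rows are per test and treat a participant's three tests as independent, which is optimistic. If the participant is the unit over all home trials, n is again 44 to 52 and the first two rows apply, now to the risk per participant.

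**How often the criterion would be met**

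The probability of zero events is (1 − p)^n, with p the risk per remote test (or per participant).

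| Assumed true risk p | n = 44 | n = 52 |
|---|---|---|
| 0.5% | 80% | 77% |
| 1% | 64% | 59% |
| 2% | 41% | 35% |
| 3% | 26% | 21% |
| 5% | 10% | 7% |

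**Participants needed, for scale**

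The number of event-free participants that brings the one-sided 95% limit down to 5%, 3%, 2% or 1% is ln(0.05)/ln(1 − limit), rounded up: 59, 99, 149 and 299.

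**The two vocabularies side by side**

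The hypothesis uses serious. Table 2 and the analysis text use minor and serious. First Trial and Textbox 5 use five grades, none of them named minor or serious. No passage links the two sets.

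**The case against.** The strongest reply is that the protocol contains no decision rule. Objective 3 states a hypothesis with a gloss, and the analysis is descriptive. That stands. A reader might infer that the test will formally be declared safe if no event occurs, but no passage says so.

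Several other stronger readings also go further than the text allows:
- **That zero events is likely even at a risk of several percent.** It is not: at n = 52 the chance is 21% at 3% and 7% at 5%.
- **That the remote test is unsupervised.** Under Second and Third Trials and the mitigation strategies, a therapist attends by video, and another person is present and told how to react in an emergency.
- **That the protocol claims equal safety under both modes.** The phrase on supervision follows the satisfaction clause and may or may not govern the safety clause, although the objective itself names both modes.
- **That only the remote tests count.** All three home trials bear on safety at home, and the pooled limit is about a third of the remote-only one. Pooling depends on independence within a person, and it says nothing specific about remote monitoring.
- **That severity can be settled after the fact.** Textbox 5 fixes a graded list in advance and all events are to be reported, so a reader can judge severity. Only the serious label is left open.

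It is also fair to say that interval methods for event proportions usually belong in an analysis plan, which is not shown here. Their absence alone is no finding. What remains is printed in the protocol: a definition of safe as no serious event, an unqualified statement about power, and a deciding term with no link to the study's own grading.

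**Conclusion.** The point holds in this limited form. Taken at its word, the hypothesis would treat zero serious events as safety. With the planned numbers, that result would exclude only risks above 5.6–6.6% per remote test (one-sided 95%; two-sided 6.8–8.0%). Over all home tests it would exclude risks above about 1.9–2.2% per test, one-sided, if tests within a person were independent. The statement about sufficient power is not supported for the safety part of objective 3. The term 'serious' needs to be reconciled with the grades.

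The limits assume no events, 44 to 52 participants and binomial sampling. The probabilities of meeting the criterion rest on assumed true risks. The sample size of 52 is not in question for its ICC purpose.

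**What to change.** 1. Reconcile the minor/serious wording in the hypothesis, Table 2 and the analysis text with the five grades, and record the mapping before any study 2 events are reviewed. Which grades count as serious is for the investigators to decide.
2. Report the number of participants with events by grade, by supervision mode and over all home trials. Give exact (Clopper-Pearson) limits with the participant as the unit, and say in advance whether they are one- or two-sided.
3. Replace the zero-event definition of safe with a bounded statement: *no serious event observed; rates above x% excluded*. With 44 participants and a two-sided 95% interval, x would be 8.0. If events occur, the same method gives the estimate and its interval.
4. Limit the power statement in Strengths and Limitations to the objectives for which a calculation was made.

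The cost is a few sentences and one table, with no change to recruitment, visits or procedures. The downside is a more modest safety statement.
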